### Sample size

Sample size was calculated for BMI at 12 months of age. Karmaus et al. [54] observed an increase in BMI of 1.65 kg/m^2^ in offspring of mothers having maternal serum levels of DDE of 1.5 – 2.9 μg/L compared to offspring of mothers having levels of < 1.5 μg/L DDE. Smink et al. [36] measured the HCB in cord blood and related this to BMI at the age of 6 years. Children with levels higher than 1.03 ng/mL HCB had a BMI which was 0.95 kg/m^2^ higher than that of children with levels lower than 0.46 ng/mL HCB. Karmaus et al. did not measure DDE in cord blood and they only measured BMI in the offspring at adult age. Smink et al. on the other hand did measure BMI in children and determined exposure to HCB in cord blood. Therefore we considered a difference in BMI of 1.0 kg/m^2^ relevant.

Previous measurements of BMI in 12 month old Dutch children [55], showed that the variation in BMI among those children is 1.36 kg/m^2^ (1 SD). Furthermore, based on data on DDE levels that already have been obtained in a Belgian cohort [56], we expect that about 30 % of our sample will have DDE levels of < 1.5 μg/L in cord blood.

In order to determine the required sample size for the present study, we entered two rows of data in Microsoft Excel (one with 30 zero’s and one with 70 ones to resemble the estimated distribution of DDE levels dichotomised at 1.5 μg/L). Thereafter we simulated BMI scores to these rows. For the 30 observations, we sampled from a population with a mean BMI of 17.1 (average BMI of boys and girls aged 12 months [55]) and SD of 1.36 and for the 70 observations we sampled from a population with a mean BMI of 18.1 and SD of 1.36. The mean BMI of this latter population is the mean BMI in Dutch boys and girls at the age of 12 months, increased with 1 BMI point. For both groups we selected a sample that resembled the population parameters and we entered those data into SPSS 17. In the following step we conducted a regression analysis with the group variable as independent and BMI scores as outcome. This linear regression analysis resulted in an r^2^ of 0.11. Finally, this r^2^ was used to conduct a sample size calculation for multiple linear regression analysis in STATA 10.0. Assuming a change in r^2^ by adding DDE levels to the model of 0.11, an alpha of 0.05, a power of 0.80 and 10 variables in the final model, the sample size needed is 42. A more conservative estimate of change in r^2^ of 0.05 resulted in a sample size of 88.

The drop-out rate in the study of Karmaus et al. was 55 % [54]. Koletzko et al. [57] followed infants from birth until they were 2 years of age. The drop-out rate was approximately 40 % during the course of that study. To ensure the highest possibility of good statistical power, the sample size in the present study for this outcome is set to *N* = 200. However, experience has indicated that from all participants, only 40 % provides a complete set of body samples. Moreover, from many participants, the volume of the cord blood is too low to be used for measurement of the selected chemicals. For this reason, we would like to extend the sample size to 500 in order to have samples available for 200 participants. Data from participants for whom no samples have been collected, will be used for other purposes than environmental chemical and health outcome associations. Currently over 300 mother-child pairs have been included, which is comparable to several other studies conducted on early life environmental chemical exposure and neurodevelopment in children [58–61].

### Statistical analyses

For all analyses effect modification of the outcome by gender will be checked, as the included chemicals disrupt the endocrine system, and in particular steroid hormones. Linearity of exposure markers and outcome will furthermore be checked due to suspected nonmonotonic dose-response associations [62]. Next to that, various methods will be considered for dealing with exposure values below the limit of quantification (LOQ), including replacement by LOQ/√2 [63], and multiple imputation [64].

In order to quantify the relation between exposure and BMI at the age of 12 and 18 months, we will use linear multilevel (mixed) models. These models take into account the dependency of repeated measures within the individuals. For each compound a separate model will be composed for weight, height, BMI, and head circumference. Exposure quartiles, time, and gender will be added to the models as fixed effects and a random effect will be added for subject. Various covariates, described in 2.5.1, will be tested and included in the model if significant (change in β-coefficient > 10 %).

To study the relationship between exposure and behavior at the age of 18 months, linear regression analyses will be conducted. Both syndrome and DSM-oriented scales from the CBCL will be used for analysis. Syndrome scales are: Emotionally Reactive, Anxious/Depressed, Somatic Complaints, Withdrawn, Attention Problems, Aggressive Behavior, and Sleep Problems. DSM-oriented scales are: Affective Problems, Anxiety Problems, Pervasive Developmental Problems, Attention Deficit/Hyperactivity Problems, and Oppositional Defiant Problems. The overall scales ‘Externalizing’ and ‘Internalizing’, and the total score were also used.

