#### Assessment of exposure

The aim is to assess perinatal exposure. For this purpose cord blood is collected from each participant at birth. Blood samples taken from the mother are not collected for the study, as women are allowed to enter the study during any stage of pregnancy. The latest moment of inclusion is just before birth, therefore this moment is most suitable to start collection of samples. Next to that, cord blood is considered a proxy for prenatal exposure and collection is non-invasive for both mother and child. To determine postnatal exposure, mothers are instructed to collect breast milk during 1 week, starting 4 weeks after birth. Use of a breast pump is allowed, and when used, the brand of the pump is provided by the participant. Timing of breast milk collection was decided upon after feedback in a pilot study, in which mothers indicated that collection any earlier after birth was uncomfortable. Furthermore, a small piece from the fetal side of the placenta is collected for epigenetic studies, as well as a sample of vernix and meconium. Parents collect a urine sample of the child during the first week after birth, however we will aim to collect multiple urine samples of the child during early childhood. Finally, at 12 months, a saliva sample of the child is collected.

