#### Health outcomes

There are various parameters early in life which are indicators for development later in life. Birth weight for example is inversely associated with hypertension and type 2 diabetes in adulthood [28, 29], and both high and low birth weight have been associated with obesity [30, 31]. Rapid growth in infancy has been identified as an independent risk factor for childhood obesity [32, 33]. A recent study by Gittner et al. showed that children who were obese at the age of 5 years already had distinct body mass index (BMI) patterns before 12 months of age, with children who had a normal BMI at age five always having a lower BMI from age 6 months and onwards compared to children who were obese at age 5 years [34]. They furthermore showed that BMI patterns over time differed between male and female children. Childhood obesity has also been related to exposure to endocrine disrupting chemicals early in life. Several studies have observed positive associations with BMI for chemicals such as organochlorine pesticides (e.g. DDE, HCB) [7, 35, 36] and PFAAs [37], although results are not unambiguous [38, 39].

Also brain development is regulated and influenced by hormones, and especially thyroid hormones are known to be essential for normal embryonal and foetal neurogenesis [40]. EDCs are known to affect thyroid hormonal function in particular. Therefore disruption of hormonal function during specific time periods important for brain development may have many consequences and may amongst others have adverse effects on neurodevelopment. Positive associations for prenatal EDC exposure and autism spectrum disorders have been reported [41–44], however studies in this area are relatively scarce. For attention deficit hyperactivity disorder, study results seem to be more convincing of an association with early life exposure to endocrine disruptors [20].

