#### Covariates

Potential covariates were selected based on literature. Weight and length of both parents are measured by the midwife at inclusion, approximately 10–12 weeks in pregnancy. Measurement of maternal weight is repeated at 36 weeks of pregnancy to determine gestational weight gain. Gestational age is determined by means of ultrasound. Birth weight is measured by a midwife or a nurse and is obtained from registries of the midwives.

Questionnaires are administered at inclusion and the start of the second trimester to collect information on education (having a bachelor or master degree, yes or no), birth date of the mother, parity, and maternal smoking (yes or no) and alcohol intake during the first trimester (drinks per week). At inclusion, fish intake (grams per day) is determined by food frequency questionnaire which includes both frequencies and portion sizes [49]. One month after birth another questionnaire is administered to inquire on the use of medication during pregnancy, including folic acid intake (yes or no).

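### In the cord-blood growth models, a 10% change-in-estimate rule is run over a list that includes birth weight, gestational age and gestational weight gain, so it may adjust away part of the effect being studied

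*Protocol article*

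**What the plan says.** The Statistical analyses section plans a separate linear mixed model for each compound and each of weight, height, BMI and head circumference. Covariates enter by one rule: "Various covariates, described in 2.5.1, will be tested and included in the model if significant", where the criterion given in parentheses is a change of more than 10% in the coefficient. Section numbers are not printed in the text at hand, but the Covariates section follows directly and is the only one that fits the cross-reference.

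That section opens with "Potential covariates were selected based on literature". Its list covers parental weight and length, maternal birth date, education, parity, smoking, alcohol, fish intake and folic acid. It also contains:
- "Birth weight is measured by a midwife or a nurse and is obtained from registries of the midwives"
- "Gestational age is determined by means of ultrasound"
- "Measurement of maternal weight is repeated at 36 weeks of pregnancy to determine gestational weight gain"

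Nothing in the list separates confounders from variables that exposure itself may affect.

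Under Assessment of exposure, "cord blood is considered a proxy for prenatal exposure", while breast milk, collected from four weeks after birth, is the postnatal marker. The opening of Methods gives the purpose as studying how perinatal exposure affects health later in life. The Health outcomes section begins "There are various parameters early in life which are indicators for development later in life", then uses birth weight as its first example and notes its association with obesity.

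**The concern.** Birth weight, length of gestation and pregnancy weight gain are all realised during or after the prenatal exposure that cord blood stands for. If exposure alters any of them, and they in turn relate to infant growth, they lie on the path from exposure to outcome. Adjusting for them removes that path from the estimate.

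A change-in-estimate rule offers no protection. It asks only whether the coefficient moves, and a mediator moves it just as a confounder does. The more of the effect a mediator carries, the more likely the rule is to select it.

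What is at stake is the meaning of the main growth coefficients. A reader would take them as the effect of prenatal exposure on growth, when for some compounds they could be closer to the part of that effect that does not act through birth size.

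**Working it through.** No figure in the article depends on this rule, so there is none to reproduce. The check asks how often the rule would select a mediator and how far the reported estimate would then move.

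**Check 1: standardised scale, n = 200**

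The sample size is the Sample size section's target for children with usable samples. The paths are assumptions, since the article gives none: direct effect d = 0.20, birth weight to BMI b = 0.30, exposure to birth weight a varied.

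- Total effect = d + a × b. Effect after adjusting for birth weight = d.
- Shift if birth weight is always included = -(a × b) / (d + a × b).
- Simulation: fit the model with and without birth weight, keep birth weight if the exposure coefficient changes by more than 10%, and average the retained estimate.

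| a | Total effect | Shift if always adjusted | Rule selects birth weight | Mean shift under the rule |
|---|---|---|---|---|
| 0.05 | 0.215 | -0.015/0.215 = -7% | about 43% | about -5% |
| 0.10 | 0.230 | -0.030/0.230 = -13% | about 63% | about -11% |
| 0.30 | 0.290 | -0.090/0.290 = -31% | about 99% | about -31% |
| -0.30 | 0.110 | +0.090/0.110 = +82% | over 99% | about +80% |

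At n = 90 the ±0.30 rows give selection in about 95% and 97% of samples. A larger sample makes selection of a strong mediator more certain, so it does not cure the problem.

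**Check 2: the article's own BMI scale**

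Inputs from the Sample size section: a difference of 1.0 kg/m², SD 1.36 kg/m², a 30:70 exposure split and N = 200. Assumed: exposure shifts birth size by 0.4 SD, and the mediated share of the total effect varies. The true total effect is 1.0 throughout.

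| Mediated share | Rule selects mediator | Mean reported effect (kg/m²) |
|---|---|---|
| 0% | 4% | 1.00 |
| 10% | 45% | 0.94 |
| 20% | 89% | 0.80 |
| 30% | 96% | 0.70 |
| 50% | 99% | 0.50 |
| -10% | 46% | 1.07 |
| -20% | 86% | 1.19 |
| -30% | 94% | 1.29 |

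Negative shares mean that the indirect path opposes the direct one. With the mediator off the candidate list, the model returns 1.0.

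Power for a two-group comparison of 60 and 140 children is 99.7%, 96.8% and 91.6% for differences of 1.0, 0.8 and 0.7 kg/m². The harm is therefore bias in the estimate and not loss of power.

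Both checks use one exposure term, one outcome time and one candidate covariate. They show the mechanism and its plausible range, not a forecast for any compound.

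**The case against.** The strongest reply is that the target is the reviewer's inference. The article never uses the term total effect, its first aim speaks only of taking relevant confounders and covariates into account, and it describes rapid infant growth as an independent risk factor. Growth given birth size is therefore a conceivable target. This stands in part: if a direct effect is intended, the plan should say so. The stated purpose names no such restriction, however, and the total effect is its natural reading.

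A second reply concerns timing. Birth weight and gestational age precede the breast-milk sample and may be genuine confounders there. Gestational age also fixes when cord blood is drawn, so it may influence the measured marker as well as respond to exposure. Both points stand. The first limits the finding to cord-blood models; the second calls for a sensitivity analysis.

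Third, the size rests on assumed paths. That also stands: with a weak path of 0.05 the shift is about 5%, and with no mediation there is none.

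A reader might go further than the document allows:
- **Birth weight would be both outcome and covariate in the weight model.** Table 2 lists birth weight among the data collected, but the analysis text is framed around 12 and 18 months and does not put birth weight among the modelled outcomes.
- **The estimate would change sign, or collider bias is established.** Every simulated mean above stays positive. Collider bias needs an unmeasured common cause of birth size and growth, which was not examined.
- **Compounds could no longer be compared.** Adjustment sets could differ between compounds, but each is analysed individually and no contrast between compounds is a stated aim.
- **The rule fails because quartiles give three coefficients, or because a 10% change is called significant.** The first is detail that a condensed article may leave to a fuller plan. The second is loose wording, explained in its own parenthesis.

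**Conclusion.** The point holds for the cord-blood growth models. It concerns a rule the article states, not detail left to another document: the rule is applied to a list that mixes pre-exposure confounders with variables that prenatal exposure may affect. Following it may move the estimate away from the effect of exposure on later growth, in either direction.

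At the planned 200 children, the assumed paths give shifts from about -5% to -31%, and about +80% when the indirect path opposes the direct one. These figures depend on exposure affecting birth weight or gestation. The article makes that plausible but does not quantify it, so the right wording is that the rule may select mediators, not that it will.

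**What to change.** For the primary cord-blood growth models:
1. State that the total effect of prenatal exposure is the target.
2. Replace the 10% rule with one confounder set, fixed in advance from a causal diagram and drawn from pre-exposure variables already collected: parental size, maternal age, education, parity, smoking, alcohol and fish intake.
3. Leave out birth weight, gestational weight gain and gestational age. Add a sensitivity model with gestational age, because it also determines when cord blood is sampled.
4. Report any other model containing these three variables only as a labelled mediation or sensitivity analysis.

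For breast-milk exposure, birth weight and gestational age may stay as confounders.

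The cost is analysis wording, a few more degrees of freedom in some models and some additional sensitivity analyses. No new data are needed.

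### The 10% change-in-coefficient rule leaves parental weight and length unprotected in the growth models, at a modest cost in precision and in comparability across compounds

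*Protocol article*

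**What the plan says.** The Statistical analyses section plans linear mixed models for growth, with a separate model per compound for each of weight, height, BMI and head circumference. The fixed part is: "Exposure quartiles, time, and gender will be added to the models as fixed effects and a random effect will be added for subject". For all other covariates the rule is: "Various covariates, described in 2.5.1, will be tested and included in the model if significant". The bracket that follows equates significance with a change of more than 10% in the β-coefficient. Exposure in quartiles gives three coefficients, and the section does not say which one must change.

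The Covariates section introduces the candidates with "Potential covariates were selected based on literature" and starts with parental size: "Weight and length of both parents are measured by the midwife at inclusion", which it places at about 10–12 weeks of pregnancy. No sentence keeps parental size, or any other candidate, regardless of the rule.

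The Sample size section uses a change in r² of 0.11 for DDE (0.05 as the conservative value), with "an alpha of 0.05, a power of 0.80 and 10 variables in the final model, the sample size needed is 42".

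**The concern.** A change-in-estimate rule asks only whether a covariate moves the exposure coefficient. That is a question about confounding. It takes no account of whether the covariate explains variation between children, which is what narrows the interval. A strong predictor of child size that is unrelated to exposure changes the coefficient only through chance imbalance. Because the threshold is relative, such a predictor is easiest to drop when the exposure effect is large.

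Two things are at stake. One is precision: data already in hand may go unused. The other is comparability: the rule runs separately in every model. The Assessment of exposure section names 12 compounds or metabolites for cord blood and breast milk in its obesogenic list, so four growth outcomes give 12 × 4 = 48 selections per matrix. Two compounds could be adjusted for different parental variables for no reason beyond chance.

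**Working it through.** **1. The plan's own sample size.** Inputs from the Sample size section: change in r² 0.11 or 0.05, alpha 0.05, power 0.80, 10 variables. I used the noncentral F test with 1 tested df, f² = Δr² / (1 − R²_full), noncentrality N·f² and denominator df N − 11.
- No variance explained by other covariates: f² = 0.11/0.89 = 0.124 gives N = 66, and 0.05/0.95 = 0.053 gives N = 152. With 1 variable instead of 10, the answers are again 66 and 152.
- The stated 42 and 88 both appear if R²_full is about 0.455: 0.11/0.545 = 0.202 gives 42, and 0.05/0.545 = 0.092 gives 88. The article does not state this R².

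So the count of 10 carries no precision. If 42 and 88 arose this way, the precision came from an unreported R².

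**2. Ceiling on the loss.** If every predictor were dropped, the standard error would grow by about 1/√(1 − R²), where R² is the share of BMI variance explained by the predictors (assumed, since the documents give none): 1.05 at 10%, 1.12 at 20%, 1.29 at 40%.

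**3. Why the rule drops predictors.** Take n = 156, which is 200 less the 22% drop-out reported under Strengths and limitations, so 39 per quartile. Use SD 1.36 and one covariate, unrelated to exposure, that explains an assumed 10% of BMI variance.
- Covariate coefficient per SD: √0.10 × 1.36 = 0.430.
- SD of its chance imbalance between top and bottom quartile: √(2/39) = 0.226.
- SD of the resulting shift in the exposure coefficient: 0.430 × 0.226 = 0.097.
- Threshold at an effect of 1.0 kg/m²: 0.10. P(|Z| > 0.10/0.097) ≈ 0.30, so it is dropped about 70% of the time.
- Threshold at 0.68 kg/m² (half an SD, assumed): 0.068. P(|Z| > 0.068/0.097) ≈ 0.48.

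This ignores sampling error in the coefficient that sets the threshold, so it is approximate.

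**4. Simulation.** Ten covariates, three of them predictive; ordinary least squares with quartile indicators; each covariate tested singly. The comparison is with the three predictors always in the model.

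| Reading of the rule | SE relative to predictors kept |
|---|---|
| Top-versus-bottom quartile coefficient only, 10–40% explained | 3–18% larger |
| Change in any quartile coefficient, 10–40% explained | 1–4% larger |

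In sample-size terms (ratio squared) this is 1.03² = 1.06 to 1.18² = 1.39 on the first reading, and 1.01² = 1.02 to 1.04² = 1.08 on the second.

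Power on the first reading, rule versus predictors kept:
- 0.68 kg/m², n = 156: 63% v 68% (20% explained), 74% v 80% (40%).
- 1.0 kg/m², n = 156: 93% v 95% (20%), 98% v 99% (40%).
- 1.0 kg/m², n = 200: 98% v 98% (20%), 99% v 100% (40%).

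**5. Sensitivity to the assumptions.** With a covariate–exposure correlation of 0.1 (40% explained, effect 1.0, first reading), the SE is still 14% larger. With nine predictors jointly explaining 40% and correlation 0 to 0.1, it is 12–27% larger for a single binary exposure coefficient and 3–15% larger on the any-quartile reading. At the other extreme, a single covariate with correlation 0.2, a weak effect and n = 200 was dropped in only 0.1% of runs.

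**The case against.** The best defence is that the loss is small where it matters. On the any-quartile reading most true predictors survive and the SE grows by only 1–4% in the three-predictor setting. At the protocol's 1.0 kg/m², power is already high on either reading. Predictors that are correlated with exposure are largely retained. All of this stands. The documents do not show that parental size will often be dropped, only that nothing prevents it.

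A reader might infer that the 10 variables in the sample size promise a precision that the rule then removes. They do not: step 1 gives the same N for 1 or 10 variables. Nor are 42 and 88 shown to be wrong, since one unreported R² reproduces both. A reader might also infer an underpowered study. With no covariate precision at all and the conservative Δr² of 0.05, power is 90% at 200 and 81% at 156. It falls below 80% only at the drop-out rates of the two cited studies: 70% at n = 120 (40% drop-out) and 58% at n = 90 (55%).

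Two further points limit the remedy. Women may enter the study at any stage, up to just before birth, so maternal weight at inclusion can be a late-pregnancy measure taken during prenatal exposure. And confounders may properly differ by compound and outcome, so one identical covariate set everywhere would be a preference.

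It could also be said that an article leaves the covariate list to the full plan. That does not answer the point, because the article states the selection rule itself.

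**Conclusion.** The point holds as one of efficiency and comparability. As written, the rule does not protect parental weight and length, and it lets adjustment for them vary by chance between compounds. With three predictors explaining 10–40% of BMI variance, the standard error is about 3–18% larger if the top-versus-bottom coefficient decides and 1–4% larger if any quartile coefficient counts. The power loss is up to about 6 points at an assumed 0.68 kg/m², and at most about 3 points at 1.0 kg/m² with 156 or more children.

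These figures rest on assumed explained variance, on covariates unrelated to exposure, and on a single time point instead of the planned repeated-measures model. Which range applies depends on a reading that the article leaves open. No bias is claimed, and no stated power is shown to fail.

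**What to change.** In the Statistical analyses section, state that maternal and paternal length and weight stay in every growth model regardless of the change in β; gender is already there. Use the 10% rule, if at all, only to add confounders and never to remove these predictors. If it is kept, say which quartile coefficient it applies to, and drop the word significant for a criterion that is not a test. For women included late in pregnancy, treat maternal weight separately, for example with a sensitivity analysis that leaves it out. It would also help to report the R² assumed for the other covariates in the sample size calculation.

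The cost is a sentence or two and a few degrees of freedom, with no new data. Missing paternal measurements need a stated handling, so that forcing these variables in does not lose children from the analysis.
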